#### Other outcomes of interest

Amount of administered coagulation factors: prothrombin complex concentrate (Beriplex®), calcium, Cyklokapron (tranexamic acid), fibrinogen, factor XIII (Fibrogammin®), phytomenadione (Konakion®), antithrombin (Kybernin®) and eptacog alfa (NovoSeven®)Estimate of costs for transfused blood products during 48 h of follow-up (see Additional file 1: Table S1) by study group

#### Deviation(s) from the original statistical plan

If substantial deviations of the analysis as outlined in these sections are needed for whatever reason, the protocol will be amended. All deviations of the analysis from the protocol or from the detailed analysis plan will be listed and justified in a separate section of the final statistical report.

### Handling of missing data and drop-outs

The number of dropouts and missing data for the primary and secondary endpoints will be low as the necessary information will be captured during the hospital stay. No complicated treatment regime is in place and the observation period is only 2 days for the primary endpoint.

To assess 1-year mortality, a hospital-wide process based on the AHV number (Swiss social security number) to capture the information from the governmental registry has already been implemented. Patients without a valid AHV number will be contacted personally.

In case of missing covariates, we will apply multiple imputation techniques and perform sensitivity analysis to show that missing information does not change the results of this trial in a substantial way. The main results will be reported based on complete cases.

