### Primary outcome measure

#### Number of transfusions

This is the number of blood products (fresh frozen plasma (FFP), RBCs, platelet concentrates) transfused within the first 48 h after study allocation in both groups (Tables 2 and 3).

**Table 2 Tab2:** Baseline data assessed upon study inclusion (data prior/upon admission to ICU) to be documented *before* administration of the study drug

	***Metavision®***	***RedCap®***
Informed consent or statement of an independent physician		X
Randomisation, assignment of the group		X
Demographics^a^	X	
Admission diagnosis		X
Past medical history		X
Relevant medication prior to bleeding (1 month)^b^		X
Type of admission (medical, surgical)		X
SAPS II	X	
SOFA score	X	
Type of surgery (if applicable)		X
Cause of bleeding		X
Reason for thrombocyte transfusion		X
Amount of blood loss prior to ICU admission	X	
Vital parameters^c^	X	
Lowest temperature measured^d^	X	
Lowest temperature measured		
Fluid balance^e^	X	
Full blood count and chemogram^f^	X	
Coagulation laboratory^g^	X	
Platelets function analysis (VerifyNow® ADP test) *before* administration of the study drug		X
Number of given RBCs	X	
Number of given FFPs	X	
Number of given platelet concentrates	X	
Amount of prothromblex	X	
Amount of tranexamic acid	X	
Amount of fibrinogen	X	
Name/amount of other given coagulation products^h^	X	
Transfusion-related side effects (AE, SAE)	X	
Thromboembolic events	X	

^a^Age, sex, BMI, height, social security number (identification log only)

^b^NOACs, antiplatelet agents and oral anticoagulation such as Marcumar® (phenprocoumon), Eliquis® (apixaban), Lixiana® (edoxaban), Xarelto® (rivaroxabam), Pradaxa® (dabigatran), Aspirin ® (ASS) and Plavix® (clopidogrel)

^c^Blood pressure, pulse, SpO_2_, ScvO_2_, SvO_2_ and respiratory rate

^d^Lowest temperature measured before ICU admission

^e^In surgical patients from anaesthesia induction until ICU admission; non-surgical patients: fluid balance (if available) upon ICU admission

^f^Hemoglobin, leucocytes, erythrocites, haematocrit, mean corpuscular volume (MCV), mean corpuscular haemoglobin (MCH), mean corpuscular haemoglobin concentration (MCHC), red cell distribution width (RDW), thrombocytes, quick, international normalised ratio (INR), activated partial thromboplastin time (APTT), thrombin time 1 (TZ1), fibrinogen and β-subunit of human chorionic gonadotropin (βHCG) in female study participants of reproductive age < 45 years

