^g^Including von Willebrand factor ristocetin cofactor (VWF:Rco); factors II, V, and VII; INR; and platelets count and level of thrombin

^h^Beriplex, Cyklokapron, Konakion, Kyberin, Fibrogammin, NovoSeven, ionised calcium, etc. (see Additional file 1: Table S1)

**Table 3 Tab3:** ICU follow-up data to be assessed within the 48-hour study period beginning at study drug administration

	***Metavision®***	RedCap®
Administration of study medication (or placebo)		
Platelet function analysis (VerifyNow® ADP test) 30–60 min after administration of study drug		X
Check if informed consent is possible		X
Amount of blood loss since drug administration		X
Cause of bleeding (if occurred)		X
SOFA score	X	
Vital parameters^a^	X	
Lowest temperature measured^b^		X
Acidosis occurred (pH < 7.35)		X
Duration of acidosis		X
Full blood count^c^	X	
Coagulation laboratory^d^	X	
ROTEM	X	
Level of vWF and FVIII	X	
Haemoglobin concentration	X	
Fluid balance^e^	X	
Number of given RBCs	X	
Number of given FFPs	X	
Number of given platelet concentrates	X	
Amount of Prothromblex after study intervention	X	
Amount of tranexam acid after study intervention	X	
Amount of fibrinogen after study intervention	X	
Name/amount of other given coagulation products^f^	X	
Number of revision surgery for haemorrhage control		X
Transfusion-related side effects (AE, SAE, see 3.7)^g^		X
Thromboembolic events		X
Any recurrent bleeding such as cerebral haemorrhage, DIC		X

^a^Blood pressure, pulse, SpO_2_, ScvO_2_, SvO_2_ and respiratory rate

^b^Lowest temperature measured since ICU admission

^c^Hemoglobin, leucocytes, erythrocites, haematocrit, mean corpuscular volume (MCV), mean corpuscular haemoglobin (MCH), mean corpuscular haemoglobin concentration (MCHC), red cell distribution width (RDW), thrombocytes, quick, international normalised ratio (INR), activated partial thromboplastin time (APTT), thrombin time 1 (TZ1), and fibrinogen^d^ including factors II, V and VII; INR; platelets count; and level of thrombin

^e^Since ICU admission until 48 h after the study drug administration

^f^Beriplex, Cyklokapron, Konakion, Kyberin, Fibrogammin, NovoSeven, ionised calcium, etc. (see above)

^g^48-h observation period

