### Determination of sample size

A total of 120 (each group 60) patients are needed to detect a 50% reduction of the number of blood products subsequently transfused within two days in patients with Wilate® compared to placebo. The sample size is calculated for a power of 80 % and a significance level of 5% for an estimate of the treatment effect evaluated with a negative binomial regression. To improve the precision of the treatment effect, the following covariates will be included: blood loss, number of blood products transfused within 12 h before administration of the study drug, anticoagulants administered 7 days before, the site of bleeding and the level of thrombocytes at baseline. The sample size calculation is based on a simulation applying resampling techniques on historical clinical data of 150 USB patients that meet the inclusion criteria.

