### Planned analyses

#### Datasets to be analysed, analysis populations

All analyses are intention-to-treat analyses. All patients included in the trial will be analysed unless informed consent is withdrawn retrospectively. The description of the dataset is described elsewhere.

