#### Primary analysis

Evaluation of the effect of Wilate® compared to placebo on the outcome number of blood products (TC, EC, FFP) administered using negative binomial regression. The following covariates will be included: blood loss, number of blood products transfused within 12 h before administration of the study drug, anticoagulants 7 days before, the site of bleeding and the level of thrombocytes at baseline.

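### The main result is set on complete cases of a five-covariate model, which conflicts with the promised intention-to-treat analysis of all included patients; the blood-loss covariate also lacks a pre-dose time point

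*Protocol article*

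**What the plan says.** On who is analysed, *Datasets to be analysed, analysis populations* says: "All analyses are intention-to-treat analyses. All patients included in the trial will be analysed unless informed consent is withdrawn retrospectively". *Patient withdrawal* likewise keeps incompletely followed patients in the intention-to-treat analysis, whatever the reason, apart from ex-post withdrawal.

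On the model, *Primary analysis* specifies negative binomial regression and says: "The following covariates will be included: blood loss, number of blood products transfused within 12 h before administration of the study drug". The list goes on to anticoagulants in the preceding 7 days, site of bleeding and baseline thrombocyte level, five covariates in all.

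On missing data, *Handling of missing data and drop-outs* plans multiple imputation and sensitivity analysis for missing covariates, then closes with: "The main results will be reported based on complete cases". It expects little missing data for the primary and secondary endpoints. It gives no expectation for covariates.

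On size, *Determination of sample size* says: "A total of 120 (each group 60) patients are needed to detect a 50% reduction of the number of blood products subsequently transfused". Power is 80% at a 5% significance level, and no allowance for loss is stated.

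On blood loss, Table 2 (baseline) lists "Amount of blood loss prior to ICU admission" and Table 3 (follow-up) lists "Amount of blood loss since drug administration".

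**The concern.** A regression on complete cases drops every patient with a gap in any covariate, even when the outcome is known. The covariates are there to improve precision; discarding outcomes because a covariate is blank works against that purpose and removes randomised patients from the headline comparison. The reassurance in the missing-data section concerns endpoints, whereas blank covariates are what would trigger exclusion here.

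This is not a detail left to the analysis plan. The protocol states the rule, and *Deviation(s) from the original statistical plan* requires an amendment for substantial departures.

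The covariate definitions add to the problem. Blood loss has no time point in the model, and one of the two listed measurements, loss after study drug, is a secondary outcome. Adjusting for it would remove part of the effect under test. Site of bleeding may not apply to every patient, since eligibility does not require severe bleeding, and a blank there would exclude the patient.

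**Working it through.** **1. The two rules applied to one patient.** Take a randomised patient with a recorded 48 h transfusion count, no withdrawal of consent, and one covariate blank.

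- Analysis-population and withdrawal sections: analysed.
- Missing-data section: not in the main result.

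Both cannot hold for the primary analysis.

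**2. The plan's 120.** Inputs from *Determination of sample size*: 60 per arm, rate ratio 0.5, power 80%, significance level 5% (two-sided assumed; sidedness is not stated). The control mean μ0 and dispersion k are not given, because the number came from resampling 150 historical patients. The usual Wald formula is

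n per arm = (1.960 + 0.842)² × [1/μ0 + 1/(0.5 μ0) + 2k] / (ln 0.5)².

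Setting n = 60 makes the bracket 60 × 0.4805 / 7.849 = 3.673, so k = (3.673 − 3/μ0)/2. This gives k = 1.09, 1.46, 1.59 and 1.69 at μ0 = 2, 4, 6 and 10. So 120 is attainable under plausible inputs but can be neither reproduced nor refuted. Below it is taken to give exactly 80%.

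**3. Power after a proportion d is dropped.** Power = Φ(2.802 × √(1 − d) − 1.960), assuming the loss is even across arms. Enrolment needed to keep 80% is 120/(1 − d), rounded up. Each d is an assumption.

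| d | Patients left | Power | Enrolment needed |
|---|---|---|---|
| 2% | 117.6 | 79.2% | 123 |
| 5% | 114 | 78.0% | 127 |
| 10% | 108 | 75.7% | 134 |
| 15% | 102 | 73.3% | 142 |
| 20% | 96 | 70.7% | 150 |

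Power falls below 78% at about 4.9% loss, below 75% at about 11.6% and below 70% at about 21.4%.

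**4. From gaps per covariate to patients lost.** If each of five covariates is missing independently in a proportion p, the loss is 1 − (1 − p)⁵. For p = 1%, 3% and 5% that is 4.9%, 14.1% and 22.6%, with power 78.0%, 73.8% and 69.3%. If the gaps fall in the same patients, the loss is only p: at 3% and 5%, power is about 79% and 78%.

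**5. Simulation check.** Unadjusted negative binomial fits, 1,000 runs per setting (Monte Carlo standard error about √(0.8 × 0.2/1000) = 1.3 points), gave:

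- μ0 = 4, k = 1.46: 81%, 76% and 73% at 60, 54 and 48 per arm.
- μ0 = 6, k = 1.59: 80%, 79% and 72%.

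This agrees broadly with step 3.

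**6. Covariates against Tables 2 and 3.**

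- Blood loss: no window in the model. The tables list loss up to ICU admission and loss after study drug; neither names the interval on the ICU before dosing.
- Anticoagulants: 7 days in the model, 1 month of medication in Table 2. The shorter window lies inside the longer one and can be derived if dates are kept.
- Site of bleeding: the tables list cause, not site.
- Prior products: no 12 h window is shown, but the counts are exported from the patient data system and may be time-stamped. No mismatch is shown.
- Thrombocytes: collected at baseline.

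**The case against.** The strongest reply is that the preferred analysis is already in the plan. Multiple imputation and sensitivity analysis are promised, so the dispute is only about which of two named analyses is the headline. That is true, and it makes the repair cheap, but the headline result is the one the intention-to-treat promise governs.

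A reader might infer that the trial loses its 80% power. The document does not support that. It gives no missingness rate for covariates; several of them (pre-ICU blood loss, product counts, blood count) are marked for direct export from the clinical system; and gaps may well overlap. Below about 5% loss the drop is under 2 points. Whether the historical resampling already reflected gaps cannot be checked.

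A reader might also infer bias. It is possible but not demonstrated: Table 2 items are documented before study drug under blinding, so dropping patients for blank items does not by itself unbalance the arms.

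Four further inferences go too far:

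- That loss on the ICU before dosing is recorded nowhere. Table 1 schedules bleeding information at screening, although it does not itemise volume.
- That post-drug loss will be used as a covariate. Three of the other covariates are explicitly pre-treatment or baseline, which points the other way; the wording merely fails to exclude it.
- That analysing blood loss in a similar way to the primary endpoint is circular. With pre-dose loss as the covariate it is ordinary baseline adjustment.
- That the medication field must be narrowed to 7 days. The 1-month record contains the needed window, and narrowing it would discard information.

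Ex-post withdrawal of consent is an openly stated exception and is no part of the contradiction.

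**Conclusion.** The conflict between the complete-case main result and the intention-to-treat commitment is real and follows from the text alone. Any randomised patient with an observed outcome and a missing covariate is both inside and outside the primary analysis.

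Its size is conditional. The 120 carries no stated margin for this loss, so if it gives exactly 80%, any loss lowers power. The 5% to 20% range, giving about 78% down to 71%, rests on assumed loss rates, a two-sided test and even loss across arms.

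The missing pre-dose time point for blood loss is a secondary but genuine gap in the primary model. The anticoagulant and bleeding-site items need definition, not new data collection on the evidence shown.

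**What to change.** In *Handling of missing data and drop-outs*, make the main analysis include every randomised patient with outcome data, except those whose consent is withdrawn retrospectively. Use the multiple imputation already planned there for missing baseline covariates, and move complete cases to sensitivity. With that change, missing covariates alone call for no increase over 120.

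In *Primary analysis* and *Determination of sample size*:

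- State that the blood-loss covariate is measured before study drug, name the window, and say that loss after study drug is never adjusted for. Any clearly pre-dose window will do; Table 2 should then list it.
- Derive the 7-day anticoagulant covariate from the 1-month medication record, keeping dates.
- Code bleeding site so that patients without an applicable site have a valid category and are not treated as missing.

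The cost is wording, a protocol amendment before database closure, and possibly a clarified Table 2 item. The one statistical downside is small: the main result then relies on an imputation model for baseline items, which the complete-case sensitivity analysis would help to check.

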## Data registration

Data will be entered into a web-based electronic case report form or directly exported from the PDMS systems. Paper case report forms will be used in parallel in case of possible technical difficulties.

## Data handling and management

All data from this study will be kept within the Investigator Site File, and only the study team will have access. In case of a patient’s ex-post denial of study participation, the data collected will not be used for publication involving either the corresponding trial or future trials. In such cases, the data will be destroyed. If the patient does not disagree, data collected until the time point of withdrawal will be used for analysis, but no further data will be collected.

The final trial data for this protocol can be supplied on request. All study data will be archived in a designated place on our intensive care unit at the University Hospital of Basel for a minimum of 10 years after study termination or premature termination of the clinical study.

## Monitoring

Monitoring will be provided by the Department of Clinical Research of the University Hospital Basel.

Monitoring will commence with the study initiation visit, followed by regular monitoring visits within time frames that will have to be determined in the monitoring plan. A member of the study team will conduct at least weekly monitoring of eCRF performance.

The source data/documents are accessible to monitors and questions are answered during possible monitoring.

## Ethical justification

Due to the nature of the condition investigated (severe bleeding representing an emergency setting), patients eligible for study participation will not able to give their consent in most cases. As described above, we will seek the patient’s approval for use of collected data for our publication as soon as feasible.

Severe bleeding is a serious condition calling for immediate intervention. Because ICU length of stay is associated with patient morbidity and mortality we chose to investigate a therapeutic approach that might reduce the need for transfusion products and their possible side effects, thus, leading to shorter ICU and hospital stays and overall better outcomes.

By achieving our goal, we may positively influence patient well-being and enhance satisfaction after severe medical conditions and, most importantly, promote a reduction in patient morbidity and mortality. This in turn would have a positive impact on our society and on the economy.

## Enrolment

The study is planned to begin in March 2021 and will continue for a 3-year period including follow-up.

## Study management and organisation

The study will be organised and managed by the research team of the intensive care unit, University Hospital of Basel. Co-enrolment of study participants in other clinical trials without interventional drug use is basically allowed but will have to be discussed among the competing research teams prior to randomisation.

## Insurance

Insurance will be provided by the sponsor through the liability insurance of the University Hospital of Basel. A copy of the certificate is filed in each trial master file and investigator site file.

## Data sharing and publication

The study results will be communicated to the individual patient when he or she regains the capacity to give study consent. During the ongoing study and until publication, there will be no public access to the data. The datasets analysed during the current study and statistical code are available from the corresponding author upon reasonable request, as is the full protocol or other study documents (e.g. informed consent forms). We plan to publish the data in an open-source major peer-reviewed clinical journal.

A public description of the study in German is available on the Swiss National Clinical Trial Portal (SNCTP).

## Timeline

**Table Taba:** 

2020–2021	- Approval from the competent ethics committee and Swissmedic - Study registration - Funding application - Establishment of eCRF - Development of a monitoring plan - Medical staff study training
2021–2024	- Inclusion of 120 patients - Follow-up of 120 patients - Annual safety report
2024	- Data analysis - Writing and submission of the manuscript for publication

## Discussion

The Will-Plate trial aims to collect innovative data on the effect of adding Wilate ® to platelet concentrates in critically ill patients with respective bleeding. There is limited but promising evidence for improvement of platelet function when additional vWF is given, thereby reducing the need for blood products when compared to placebo. In our study, we aim to confirm the superiority of vWF over placebo for the management of severe blood loss based on high-quality data. The results of this study may lead to better algorithms for the treatment of severe bleeding, which could improve clinical care for patients, reduce the burden of family members and protect the patient’s long-term autonomy and health.

## Patient/public involvement

Patients or the public were not involved in the design of our research and will not be involved in the conduct, reporting or dissemination of our research. This study was registered at the Swiss National Clinical Trial Portal (SNCPT) for official discretion.

## Data Availability

NA.
